| Primary
To assess the safety, tolerability and reactogenicity profile of a prime-boost regimen (with an interval between prime and boost of 28 OR 112 days in 12-17 year olds, and interval of 112 days in 6-11 year olds) of the candidate vaccine ChAdOx1 nCoV-19 ( $5.0 \times 10^{10}$ vp / $5.0 \times 10^{10}$ vp) in children aged 6-17 years. | a) occurrence of solicited local reactogenicity signs and symptoms for 7 days following vaccination;
b) occurrence of solicited systemic reactogenicity signs and symptoms for 7 days following vaccination;
c) occurrence of unsolicited adverse events (AEs) for 28 days following vaccination;
d) occurrence of SAEs and disease enhancement episodes
e) occurrence of abnormal laboratory findings (Grade 3 and above) | a)-c) as stated, d) throughout the study, e) D2 and D7 post-boost blood tests (safety bloods) |
| Secondary
To assess cellular and humoral immunogenicity of ChAdOx1 nCoV-19 ( $5.0 \times 10^{10}$ vp / $5.0 \times 10^{10}$ vp) given as homologous prime boost (at 28 and 112 days post prime in 12-17 year olds, and 112 days post prime in children aged 6-11 years)                                                                               | a) Quantify antibodies against SARS-CoV-2 spike protein (seroconversion rates)
b) Virus neutralising antibody (NAb) assays against live and/or pseudotype SARS-CoV-2 virus
c) Interferon-gamma (IFN- $\gamma$ ) enzyme-linked immunospot (ELISpot) responses to SARS-CoV-2 spike protein
d) cell analysis by flow cytometry assays                                                                                            | Blood samples drawn at D0, D28, D56, , D84, D112, D140, D182 and 364                          |

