### 7.3. Blood tests

Safety bloods will be taken for a subset of up to 40 participants in groups 3 and 4, as outlined in tables 5b and 5d. These will include a full blood count, urea and electrolytes, liver function tests, CRP, clotting screen and D-dimer. Reference ranges will be in accordance with local NHS guidelines. Abnormalities occurring outside this range will be graded in severity and those scoring a grade 3 or above will be classified as an AE.

Immunology; Immunogenicity will be assessed by a variety of immunological assays. This may include antibodies to SARS-CoV-Spike and non-Spike antigens by ELISA, ex vivo ELISpot assays for interferon gamma and flow cytometry assays, neutralising and other functional antibody assays and B cell analyses, virus neutralising Ab (NAb) assays against live and/or pseudotype SARS-CoV-2 virus. Other exploratory immunological assays including cytokine analysis and other antibody assays, DNA analysis of genetic polymorphisms potentially relevant to vaccine immunogenicity and gene expression studies amongst others may be performed at the discretion of the Investigators. Further exploratory immunology assays may be performed at the discretion of the Investigators on HIV and non-HIV cohorts, including, but not limited to: T cell Proliferative responses to SARS-CoV-2 antigen; T cell cross-reactivity to circulating common cold coronaviruses; Multiparameter immunophenotyping by CyTOF; BCR and TCR repertoire analysis; Serum analysis by Luminex (including inflammatory, anti-inflammatory and adaptive cytokines, chemokines, growth factors and antimicrobial proteins); HIV viral reservoir; amongst others.

Collaboration with other specialist laboratories in the UK, Europe and outside of Europe for further exploratory tests may occur. This would involve the transfer of serum or plasma, PBMC and/or other study samples to these laboratories, but these would remain anonymised. Informed consent for this will be gained from participants. This would be in line with the national guidance and policy for submitting samples for testing at reference labs. Immunological assays will be conducted according to local SOPs.

Participants or their parent/guardian will be informed that there may be leftover samples of their blood (after all testing for this study is completed), and that such samples may be stored indefinitely for possible

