#### 7.4.3. Subsequent visits:

Follow-up visits will take place as per the schedule of attendances outlined in Tables 5a-d, with their respective windows. Safety bloods will be conducted in a subset of participants aged 6-11 years (to be determined by the sites); up to 40 participants will be allocated to have safety bloods taken at one of V3a, V3b, V4a or V4b, resulting in 6 study bloods being taken for this subgroup.. Participants will also have safety bloods taken on the day of the booster. This is to ensure accurate interpretation of any abnormal safety blood findings.

Participants will be assessed for local and systemic adverse events, interim history, physical examination, if required, review of diary cards (paper or electronic) and blood tests at these time points as detailed in the schedule of attendances. Blood will also be taken for immunology purposes and a booster vaccination given at Visit 2.

If participants experience adverse events (laboratory or clinical), which the investigator (physician), CI and/or DSMB chair determine necessary for further close observation, the participant may be admitted to an NHS hospital for observation and further medical management under the care of the Consultant on call.

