| Physical assessment (as required)          |                                        | X                           | X                   | X                 | X                                     |               |                | X                 | X                   |
| Vaccination                                |                                        | X                           |                     |                   | X                                     |               |                |                   |                     |
| Safety bloods Group 3 subset only (n=20)   |                                        |                             |                     |                   | X – if allocated to V4a or V4b (n=20) | X             | X              |                   |                     |
| COVID-19 immunogenicity bloods             |                                        | X                           | X                   | X                 | X                                     |               |                | X                 | X                   |
| Diary card review                          |                                        |                             | X                   | X                 | X                                     |               |                | X                 |                     |
| AE/SAE check                               |                                        | X                           | X                   | X                 | X                                     |               |                | X                 | X                   |

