**Table 5d – Schedule of visits (Group 4 – D112 boost)**

|                        | Online survey to establish eligibility | V1                          | V2                | V3               | V3a* (n=10)   | V3b* (n=10)    | V4                | V5                  |
|------------------------|----------------------------------------|-----------------------------|-------------------|------------------|---------------|----------------|-------------------|---------------------|
| Study timeline         | Up to D0 - 90                          | D0                          | 84                | D112             | D2 Post Boost | D7 Post Boost  | D140              | D364                |
| Study windows          |                                        | Within 90 days of screening | Day 84-98 post V1 | D112-140 post V1 | D2-4 after V3 | D7-12 after V3 | Day 21-35 post V3 | Day 334-394 post V1 |
| Informed consent       |                                        | X                           |                   |                  |               |                |                   |                     |
| Medical history        | X                                      |                             |                   |                  |               |                |                   |                     |
| Urinary pregnancy test |                                        | X                           |                   | X                |               |                |                   |                     |

CONFIDENTIAL

|                                          |  |   |   |                                       |   |   |   |   |
|------------------------------------------|--|---|---|---------------------------------------|---|---|---|---|
| (if female > 11yrs)                      |  |   |   |                                       |   |   |   |   |
| Physical examination                     |  | X |   | X                                     |   |   |   |   |
| Physical assessment (as required)        |  | X | X |                                       |   |   | X | X |
| Vaccination                              |  | X |   | X                                     |   |   |   |   |
| Safety bloods Group 4 subset only (n=20) |  |   |   | X – if allocated to V3a or V3b (n=20) | X | X |   |   |
| COVID-19 immunogenicity bloods           |  | X | X | X                                     |   |   | X | X |

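### Primary endpoint (e) and the section 7.3 AE rule count any Grade 3 laboratory value after the boost, with no reference to the child's own booster-day sample

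*Protocol*

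**What the plan says.** Section 4 of the protocol, like the synopsis, gives primary endpoint (e) as "occurrence of abnormal laboratory findings (Grade 3 and above"), with its time points stated as "e) D2 and D7 post-boost blood tests (safety bloods"). Section 7.3 turns results into adverse events by grade alone: values outside the reference range are graded, and "those scoring a grade 3 or above will be classified as an AE".

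Section 7.4.3 says "Participants will also have safety bloods taken on the day of the booster" and gives the reason: "This is to ensure accurate interpretation of any abnormal safety blood findings". The schedules carry this through. Table 5c marks the booster visit for Group 3 as "X – if allocated to V4a or V4b (n=20") and Table 5d marks it for Group 4 as "X – if allocated to V3a or V3b (n=20"). That is up to 40 children aged 6-11, each with one post-boost safety sample at either D2 or D7. The sites determine the subset.

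Section 9.1 defines an adverse event more broadly. It admits a laboratory result that is clinically significant or that has changed from its baseline value.

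**The concern.** The protocol collects a within-child reference and says what it is for, yet the two rules that produce the count do not mention it. Neither endpoint (e) nor section 7.3 asks whether the Grade 3 value is new, has worsened, or was there before the second dose. A child who is Grade 3 on booster day and still Grade 3 at D2 or D7 satisfies both.

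These bloods were added because the DSMB thought reactogenicity might be higher in the younger cohort (section 3.2). The question they should answer is what changes after a dose. A count that cannot separate a pre-existing abnormality from one arising after the boost answers a different question. Since section 10.4 plans no significance testing for the primary safety endpoints, readers will interpret the raw count itself.

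**Working it through.** **The plan's own probability.** Section 10.1 says 60 participants give more than a 90% chance of seeing at least one event at a true rate of 5%. This reproduces: 1 − 0.95^60 = 95.4%. It does not concern endpoint (e), and no figure in the protocol depends on the point made here.

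**The rules side by side.**

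| Place in protocol | Reference to an earlier value? |
|---|---|
| Section 4 and synopsis, endpoint (e) | None: absolute grade, D2 and D7 post boost only |
| Section 7.3, AE rule | None: absolute grade |
| Section 7.4.3, booster-day sample | Yes: taken to interpret abnormal results |
| Section 9.1, AE definition | Yes: clinical significance or change from baseline |

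The booster-day sample is the only pre-boost safety sample marked in Tables 5c and 5d. Section 7.4.2 mentions safety bloods on day 0 but points to Tables 5a and 5b, which mark none. Section 10.1.1 lists the planned safety summaries and gives no counting rule for laboratory findings.

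**Illustration of size.** Inputs:
- n = 40, the maximum in section 7.4.3.
- b = chance that a child has at least one Grade 3 value on booster day. Not in the protocol; assumed 1% to 10%.
- w = share of those still Grade 3 at the post-boost sample. Not in the protocol; assumed 50% or 100%.
- v = chance of a new Grade 3 value after the boost. Not in the protocol; 2% used as an example.

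Expected carried-over cases = n × b × w. Chance of at least one = 1 − (1 − b × w)^40.

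| b | Expected, w = 50% | At least one, w = 50% | Expected, w = 100% | At least one, w = 100% |
|---|---|---|---|---|
| 1% | 0.2 | 18% | 0.4 | 33% |
| 2% | 0.4 | 33% | 0.8 | 55% |
| 5% | 1.0 | 64% | 2.0 | 87% |
| 10% | 2.0 | 87% | 4.0 | 98.5% |

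For example, b = 2% and w = 100% give 40 × 0.02 = 0.8 expected and 1 − 0.98^40 = 55%.

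The effect on the reported count, with v = 2% and w = 100%, compares the literal rate 1 − (1 − b)(1 − v) with the new-onset rate (1 − b)v, each times 40:
- b = 1%: 1.19 against 0.79
- b = 2%: 1.58 against 0.78
- b = 5%: 2.76 against 0.76
- b = 10%: 4.72 against 0.72

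On these assumptions the literal count is about double the new-onset count once b reaches 2%.

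**Can the control children supply the background rate?** If the 4:1 allocation carried over to the subset, about 40 × 1/5 = 8 children would be MenB recipients. With no events in 8, the two-sided 95% upper limit is 1 − 0.025^(1/8) = 37%. That is too wide to help.

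**The case against.** The strongest reply is that baseline handling of laboratory data, such as a treatment-emergent rule or a shift table, is usually set in the statistical analysis plan. The protocol promises a detailed one, which was not available here. If the protocol were merely silent, that would settle the matter. It is not silent: it fixes a primary endpoint and an AE classification, and as worded both admit an unchanged pre-boost value. The AE label is also applied when data are recorded, before any analysis plan operates.

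A reader might infer that the booster-day sample goes unused. The documents do not support that. Section 7.4.3 states its purpose, and section 9.9 requires pre-existing conditions and timing relative to vaccination to be weighed for every AE, so a pre-boost Grade 3 value would be visible in the causality assessment. However, endpoint (e) counts occurrence whatever the causality, so this helps interpretation and leaves the count unchanged.

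A reader might also infer that an unchanged booster-day value is itself recorded as an AE about 112 days after the prime. Section 9.10 records local and systemic AEs for 28 days after each vaccination, and a pre-boost value at D112 lies outside that window. Nor can it enter endpoint (e), which names only D2 and D7.

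The objection to the size stands. The prevalence and persistence are assumptions. The participants are healthy, and most Grade 3 limits in Table 11 lie far from normal: haemoglobin below 85 g/l, platelets below 100, CRP above 100 mg/l. The low end of the range may be nearer the truth. The D-dimer row should not be used to argue for the high end, because its normal limit (below 500 ng/ml) and Grade 3 limit (above 0.5 ng/ml) are inconsistent. That row is a separate point to be reconciled.

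**Conclusion.** The point holds as a mismatch within the protocol. Endpoint (e) and section 7.3 do not carry through the purpose given for the booster-day sample in section 7.4.3, or the baseline wording in section 9.1. Followed literally, they count a persisting pre-boost Grade 3 value as a post-boost finding. Whether the eventual analysis will do so is not established.

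The size is unknown. Under the assumed 1% to 10% booster-day prevalence in 40 children, the expected carry-over is 0.2 to 2 cases with 50% persistence and 0.4 to 4 with full persistence. These figures show sensitivity and are not estimates, and fewer than 40 sampled children would lower them in proportion. The figure of about 8 controls is likewise an assumption, because the sites choose the subset and no split by arm is stated.

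The consequence is moderate. The endpoint is descriptive, and no test or sample size rests on it. It is still a primary safety outcome in a small group, where one or two carried-over cases could change how the count is read. The change should be made.

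**What to change.** 1. In section 4 and the synopsis, define endpoint (e) as a new Grade 3 or above, or a worsening to Grade 3 or above, at D2 or D7 relative to the child's own booster-day sample.
2. Align section 7.3 with that definition and with section 9.1.
3. Report a shift table of booster-day grade by post-boost grade for each test, by vaccine received.
4. Keep a listing of every Grade 3 value with the measured results, so that nothing is hidden. This matters for a child already at Grade 3 on booster day, because Table 11 as it stands shows no Grade 4 column in which further deterioration could register. The same listing should identify children without a booster-day result, for whom new onset cannot be judged.

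The cost is a sentence in each definition, one table and one listing. The sample is already scheduled, so no extra visit or blood is needed.

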#### **7.4. Study visits**

The study visits and procedures will be undertaken by members of the clinical trials team. The procedures to be included in each visit are documented in the schedule of attendances. Each visit is assigned a time-point and a window period, within which the visit will be conducted. Visits may take place in outpatients departments or other sites which are not clinical settings such as village halls and schools as required.

##### **7.4.1. Screening process**

###### **Initial screening**

Parents/guardians or participants will be required to complete a 2-part online screening process. Firstly, they will be directed to an online questionnaire as an initial confirmation of eligibility and to screen for clear exclusion criteria. In part 2, they will be asked to indicate electronic consent for:

1. Providing details of their own or the child's s medical history
2. Permission for a telephone screening visit, if required Collection of further information from GPs where necessary, ahead of their first visit. We will aim to contact the participant's general practitioner with the permission of the participant (electronic consent) to corroborate medical history when necessary. GPs will be notified that the participant has volunteered for the study, with their parent/guardian's consent if applicable. This may require emailing confidential information to their GP and receiving medical records from their GP. This will only be done via secure NHS.net address.

###### **Telephone screening**

Where further clarification of eligibility is required, participants or their parent/guardian will be invited for a telephone screening visit. This will be recorded in a telephone screening CRF. The interval between the last screening process (whether online or telephone) and V1 will be a maximum of 90 days.

The eligibility of the participant will be reviewed electronically. Decisions to exclude the participant from enrolling in the trial will be at the discretion of the Investigator. Participants without a past medical history or drug history that requires further review may be invited directly to enrolment/vaccination visits. If eligible, a day 0 visit will be scheduled for the participant to gain informed consent, receive the vaccine and subsequent follow-up. They will also receive a link to a video with information to inform consent.

If a volunteer is not deemed eligible, their information will only be stored until the end of the trial, and this will be made clear in the PIS.

##### **7.4.2. Day 0: Completion of screening, consent**

At D0, the participant and/or parent/guardian of the participant will personally sign and date the latest approved version of the Informed Consent form. A written version and verbal explanation of the Study

Information leaflet and Informed Consent will be presented to the participant (if aged 16 and over) or their parent/guardian (if aged under 16) as well as an assent form and information leaflet for participants aged 6 and over. The following information will be covered:

- The exact nature of the study
- What it will involve for the participant
- The implications and constraints of the protocol
- The known side effects and any risks involved in taking part
- The sample handling protocol – participants will be informed that anonymised samples taken during the study may be shared with study collaborators

The Participant Information Sheet will be made available to the participant for an appropriate amount of time (where possible this will be a minimum of 24 hours) prior to consent being obtained. A consent video may also be made available to participants prior to visit 1 to assist with the consent process. The following general principles will be emphasised:

- Participation in the study is entirely voluntary
- Refusal to participate involves no penalty or loss of medical benefits
- The participant may withdraw from the study at any time
- The participant is free to ask questions at any time to allow him or her to understand the purpose of the study and the procedures involved

The participant or their parent/guardian will be allowed as much time as they wish to consider the information, and the opportunity to question the Investigator, their GP or other independent parties to decide whether they will participate in the study. Written informed consent will then be obtained by means of the participant or their parent/guardian's dated signature, and dated signature of the person who presented and obtained the informed consent. The person who obtained the consent must be suitably qualified and experienced, and have been authorised to do so by the Chief/Principal Investigator and listed on the delegation log. A copy of the signed informed consent will be given to the participant. The original signed form will be retained at the research study site.

Participants will be considered enrolled into the trial at the point of vaccination. Before vaccination/trial intervention, the eligibility of the participant will be reviewed. Pulse and temperature will be observed and if necessary, a medical history and physical examination may be undertaken. Blood will be taken for safety bloods and immunology tests as per Table 5a and b. Anaesthetic cream will be offered to all participants. Vaccinations will be administered as described below.

#### 7.4.2.1. Vaccination - D0

All vaccines will be administered intramuscularly according to specific SOPs. Observations will be taken 60 minutes after vaccination (+/- 30 minutes) and the sterile dressing removed and injection site inspected.

In all groups, participants or their parent/guardian will be given an oral thermometer, tape measure and diary card (paper or electronic), with instructions on use, along with the emergency 24-hour telephone

number on the contact card to contact the on-call study physician if needed. For participants aged under 16, it is expected that parents/guardians will communicate with the trial team by telephone and fill in the diary card. Participants aged 16 and over will be expected to fill in their own diary card and communicate with the study team directly.

Participants or their parent/guardian will be instructed on how to self-assess the severity of these AEs. There will also be space on the diary card to self-document unsolicited AEs, and whether medication was taken to relieve the symptoms. Diary cards will collect information on the timing and severity of the following solicited AEs.

In keeping with PHE guidance on vaccine associated fever during the pandemic [36], participants experiencing fever within the first 48 hours of vaccination, with no other primary symptom of COVID-19 (cough, anosmia, ageusia) will not be required to self-isolate unless there is otherwise clinical suspicion of COVID-19.

